## Abstract

**Background:**

Millions of people who need treatment for substance use disorders (SUD) do not receive it. Evidence-based practices for treating SUD exist, and some are appropriate for delivery outside of specialty care settings. Primary care is an opportune setting in which to deliver SUD treatment because many individuals see their primary care providers at least once a year. Further, the Patient Protection and Affordable Care Act (PPACA) increases coverage for SUD treatment and is increasing the number of individuals seeking primary care services. In this article, we present the protocol for a study testing the effects of an organizational readiness and service delivery intervention on increasing the uptake of SUD treatment in primary care and on patient outcomes.

**Methods/design:**

In a randomized controlled trial, we test the combined effects of an organizational readiness intervention consisting of implementation tools and activities and an integrated collaborative care service delivery intervention based on the Chronic Care Model on service system (patient-centered care, utilization of substance use disorder treatment, utilization of health care services and adoption and sustainability of evidence-based practices) and patient (substance use, consequences of use, health and mental health, and satisfaction with care) outcomes. We also use a repeated measures design to test organizational changes throughout the study, such as acceptability, appropriateness and feasibility of the practices to providers, and provider intention to adopt the practices. We use provider focus groups, provider and patient surveys, and administrative data to measure outcomes.

**Discussion:**

The present study responds to critical gaps in health care services for people with substance use disorders, including the need for greater access to SUD treatment and greater uptake of evidence-based practices in primary care. We designed a multi-level study that combines implementation tools to increase organizational readiness to adopt and sustain evidence-based practices (EBPs) and tests the effectiveness of a service delivery intervention on service system and patient outcomes related to SUD services.

**Trial registration:**

Current controlled trials: NCT01810159

**Electronic supplementary material:**

The online version of this article (doi:10.1186/s13012-015-0256-7) contains supplementary material, which is available to authorized users.

## Background

Substance use disorders (SUD) continue to be under-identified and under-treated [1]. In 2013, 22.7 million people aged 12 or older needed treatment for an illicit drug or alcohol use problem; of these, 20.2 million did not receive it [1]. The consequences of untreated alcohol and drug abuse are great and include increased risk of disease, injury, disability, and death [2,3] as well as hundreds of billions of dollars in costs to the criminal justice, social welfare, and health care systems [4-6]. Historically, treatment of SUD has taken place in residential and outpatient specialty care settings. Although specialty care settings play an important role for individuals with severe dependence, long waiting lists, stigma, and the lack of public funding for patients without insurance coverage have contributed to the lack of access. Further, many people who need treatment are not aware that they need it, are not ready for treatment, or do not know how or where to seek treatment [7].

Primary care clinics are a feasible and opportune setting in which to identify and provide treatment to people with SUD. Studies suggest that the prevalence of alcohol use disorders and use of illicit drugs is higher among primary care and emergency room patients than it is in the general population [8,9]. Further, most individuals (82%) visit a health professional at least once a year, thus providing ample opportunity for providers to identify patients in need of treatment [10]. Research suggests that integrating SUD treatment and general health care can result in less utilization of inpatient care and fewer emergency room visits [11] and that integrated care is acceptable to patients with an SUD [12].

However, despite the potential benefits of providing SUD screening and treatment in primary care and the existence of evidence-based practices (EBP) suitable for delivery in these settings [13-21], uptake of evidence-based SUD treatments in primary care has been slow. Accordingly, patients are unlikely to receive treatment for their SUD in primary care [20-24]. Some of the organizational barriers to providing SUD treatment in primary care settings include lack of insurance reimbursement, perceived lack of time to fully assess and discuss substance use, and lack of administrative buy-in for integrating SUD care into medical practices [25,26]. At the physician level, perceived barriers to SUD treatment adoption include negative attitudes toward people with SUD, lack of confidence among physicians in their ability to treat SUDs, lack of adequate role models and access to decision support consultants, and deficiencies in training and expertise in addiction treatment [13,25-28].

Research on introducing new practices into health care and other organizations suggests that intervention at both the organizational level (i.e., to increase organizational readiness to adopt new practices) and service delivery system level (i.e., reorganizing how care is provided to support the new practice) may both be necessary to integrate and sustain EBP [29-31]. Organizational readiness refers to “the extent to which organizational members are psychologically and behaviorally prepared to implement organizational change” [32]. Interventions that increase an organization’s commitment to change and the ability of the members of the organization to visualize how the new practice could be adopted and incorporated into existing practices are both important to increasing organizational readiness and adoption of EBP [33]. However, even when an organization exhibits high organizational readiness, change may not be successful unless attention is paid to how the new practice is supported and integrated into existing care practices. Further, adapting new practices to fit the nuances of a setting is a key component of whether the practice is ultimately accepted and adopted. As Damschroder et al. note, “without adaptation, interventions usually come to a setting as a poor fit, resisted by individuals who will be affected by the intervention, and requiring an active process to engage individuals in order to accomplish implementation [30].”

To address the need for change at two levels—organizational and service delivery system—to increase the intent and ability of primary care providers to identify and treat opioid and alcohol use disorders (OAUD), we designed a multi-level study to create and evaluate change at both levels. We call this study substance use motivation medication integrated treatment (SUMMIT) and focus on alcohol and opiate use disorders because of their relevance to the clinic population and availability of effective medications. At the organizational level, we test the effects of an organizational readiness intervention on the organization’s readiness to identify and treat individuals with opioid and alcohol use disorders. At the service delivery system level, we use Wagner’s Chronic Care Model [34] to reorganize and guide how care for OAUD is provided and supported; we call the service delivery intervention integrated collaborative care (ICC). Integrated, collaborative approaches have been successful in improving outcomes for patients experiencing a variety of different chronic illnesses, including diabetes [35], asthma [35], and depression [36]. ICC has improved implementation of evidence-based treatments and quality of care [37], lowered costs [38], improved patient outcomes [39-42], and is thought to be feasible for and sustainable in primary care clinics [43]. We test the effects of the organizational readiness intervention using a repeated measures pre-post design and the impact of the service delivery intervention on patient-level outcomes using a randomized controlled trial (RCT) to compare the service delivery intervention (ICC) with “service as usual” (SAU) on service system and patient outcomes. We hypothesize that provider (providers include administrators, medical and mental health providers, and other staff) readiness to implement the EBP and patient-centered SUD care will improve from the pre-organizational readiness intervention period (year 1) to the post-readiness intervention periods (years 2–5); that patients in the ICC condition will report more integrated, patient-centered evidence-based care for their opioid and/or alcohol use disorders, will be more likely to receive OAUD care, and will have lower overall health care utilization (e.g., emergency department and medical visits) than patients in the SAU condition; and that provider adoption of EBP will increase from year 2 to years 3 and 4 and that providers will still be delivering OAUD EBP a year after completion of the study in year 5. We also hypothesize that patients in the ICC condition will report less substance use, fewer SUD consequences, higher health and mental health functioning, and greater satisfaction with their SUD care 6 months after enrollment than SAU patients.

The evidence-based practices that we are introducing into the clinic are two medications—buprenorphine/naloxone (BUP/NX) (trade name Suboxone®) for opioid dependence and extended-release injectable naltrexone (XR-NTX) (trade name Vivitrol®) for alcohol dependence—and a motivational interviewing (MI)-based behavioral treatment for those with abuse or dependence of either substance. BUP/NX has been proven effective for patients with opioid (heroin as well as prescription opioid) dependence and is feasible for delivery in office-based settings [12,44-49]; XR-NTX has been found effective for people with alcohol or opioid dependence and also is feasible for delivery in primary care [50-54]. Due to greater complexity for administration for opiate dependence, in this study, XR-NTX is used only to treat alcohol dependence. MI-based interventions have improved SUD treatment outcomes [18,19,55,56].

In this article, we present our methods, including study setting; conceptual framework; study design; participant recruitment; a description of the interventions, which consist of the organizational readiness intervention and the service delivery intervention; as well as our measures, data collection procedures, and analysis plan. We conclude with a discussion of the study’s unique design and its relevance to implementation of OAUD treatment in primary care, and we note the study’s limitations.

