## Methods/design

### Study setting

We are conducting the study in a large urban, federally qualified health center (FQHC) in Los Angeles that serves approximately 20,000 patients annually. The study is taking place at the FQHC’s two largest sites. We elected to hold the study in an FQHC because of the expected influx of patients into publicly funded clinics due to expanded coverage, an increased funding and an increase in the number of clinics due to the Patient Protection and Affordable Care Act (PPACA) [57], and the greater opportunity to reach more individuals who need treatment. The clinic currently has integrated mental health services and provides treatment for anxiety and depressive disorders; however, prior to the study, the clinic did not conduct any screening or treatment for SUD. If substance misuse was identified, patients were sometimes, but not systematically, referred to specialty care.

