### Study design

The study is designed to test the combined effect of both an organizational readiness intervention (which includes a 1-year organizational preparation period and an 8-month pilot of the ICC condition study) and a service delivery intervention (see Figure 2). We examine the effects of the interventions on organizational readiness, service system, and patient outcomes, all of which are believed to be important in understanding the uptake of new practices [58]. To test the unique effects of the organizational readiness intervention on provider outcomes, we use a pre-post-intervention design and measure these outcomes at the beginning of the study and then again at the end of year 1. At the end of year 1, we implement an eight-month pilot test of ICC. During the pilot test, providers gain experience with the protocols, and the protocols are iteratively adapted and refined based on provider feedback. Because we hypothesize that readiness outcomes may continue to improve as providers gain experience with ICC and the three treatments, we continue to measure organizational readiness outcomes annually at years 2–5. Thus, changes in outcomes between year 1 and years 2–5 reflect the combined effect of both the organizational readiness intervention and ICC on provider outcomes. To test the effects of the interventions on service system and patient-level outcomes, we are conducting an RCT to compare the effects of ICC with SAU. Service-system outcomes are patient-centered collaborative care, utilization of SUD treatment, patient utilization of health care services, provider adoption of EBP, and sustainability of EBP. Patient-level outcomes include substance use, consequences of use, physical and mental health functioning, and patient satisfaction with SUD care.

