##### Service system measures

We are analyzing five service system outcomes: (1) *Patient-centered, collaborative SUD care*. We measure patient experiences using a locally developed measure based on the validated Patient Assessment of Chronic Illness Care (PACIC) [73]. Provider perceptions of collaborative SUD care are measured using the Assessment of Chronic Illness Care (ACIC) [74]. (2) *Patient utilization of SUD services*. This refers to patient linkage to and usage of appropriate treatment. We measure this by examining clinic administrative records that capture all patient encounter dates, types and providers, and by patient self-report of clinic services on the follow-up survey. (3) *Patient utilization of health care services*. This refers to utilization of emergency department and health care services. We measure this by examining clinic administrative records of clinic health care visits and by patient self-report of emergency department visits. (4) *Provider adoption of EBP*. This is a measure of provider use of the EBP (either of the medications or the brief therapy). Although adoption is sometimes thought of as an implementation (or readiness) outcome, we include it with service system outcomes because we believe that both interventions—organizational readiness and service delivery—are needed for adoption of EBP. We measure adoption by examining administrative records for prescription of either medication or use of the therapy and by asking providers to self-report use of the EBP in the survey. (5) *Sustainability of EBP*. This is the extent to which the three EBP are still being utilized during year 5 of the study. Following the end of patient enrollment in the RCT, we will continue to monitor clinic practices to examine whether the EBPs are still being utilized following the end of the RCT.

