##### Analysis plan

Our quantitative analysis of provider survey items and administrative data related to service system outcomes will consist of pre-post, one-way repeated measures ANOVA comparisons of survey responses between pre- and all post-intervention periods. To analyze patient-level outcomes, we use an intent-to-treat approach. We will first conduct a bivariate analysis to estimate the uncontrolled association between being in the ICC group and outcome. In addition, even though our design randomly assigns patients, we will assess any possible imbalance in covariates between ICC and SAU groups including age, gender, race/ethnicity, and education that affect the impact of the ICC intervention on the outcomes. In cases where observed imbalances are attributable to sample attrition, we will correct for potential bias due to attrition at follow-up using response weights. In addition, characteristics related to an outcome at a conservative significance level of α = 0.2 will be considered covariates in a multivariate analysis for reduction of bias if imbalanced or for efficiency gains. For the multivariate analyses, we will infer about the impact of ICC on an outcome by fitting hierarchical models using SAS Proc Mixed, R LME4, and Winbugs. These models take into account the multi-level structure of the data: two repeated measures over time (baseline and 6 months) nested within patient and patients nested within clinics. Sensitivity analyses will be conducted testing model functional forms, the covariates to be used, and the impact of influential outliers in the analyses results. For outcomes assessed only at month 6 (e.g., treatment satisfaction), we will use cross-sectional analyses (such as linear and logistic regression) to estimate the effect of ICC relative to SAU. This study was designed to estimate sufficient effect sizes that can be detected with a power of at least 80% when comparing the outcomes of patients randomly assigned to the two conditions in an end-status analysis at month 6 for a 5% significance level. For continuous outcomes, the study will be able to detect effect sizes of about 0.30–0.32 standard deviations. These are the kind of effects that can be expected for an intervention like ICC [42]. For dichotomous outcomes, we will be able to detect a difference of 13–14 percentage points under the assumption that the SAU group has a 15% rate of receiving the outcome.

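### Provider adoption is hypothesised to grow from year 2 to years 3 and 4, but the only stated test compares the pre-period with all post periods and does not address that growth

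*Protocol article*

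**What the plan says.** In the Background, the protocol article uses two reference periods in its provider hypotheses. Readiness and patient-centered care are to improve from the "pre-organizational readiness intervention period (year 1") to years 2 to 5. Adoption has a different reference: "provider adoption of EBP will increase from year 2 to years 3 and 4". A separate clause expects the practices still to be in use in year 5.

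Service system measures lists provider adoption as outcome (4), taken from administrative records and provider self-report. Sustainability is outcome (5): "This is the extent to which the three EBP are still being utilized during year 5 of the study".

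The Analysis plan under Service delivery intervention gives one method for provider-survey and administrative service system data: "pre-post, one-way repeated measures ANOVA comparisons of survey responses between pre- and all post-intervention periods". The same phrase describes the readiness analysis in the earlier Analysis plan, under Organizational readiness intervention.

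On the starting level, Study setting says that "prior to the study, the clinic did not conduct any screening or treatment for SUD". The Background says that the study introduces the two medications and the motivational therapy, and Study design starts the eight-month pilot at the end of year 1.

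**The concern.** The comparison of year 1 with later years fits the readiness hypothesis. Carried over to adoption, it changes the question. The hypothesis asks whether use grew once the practices were available. The stated comparison asks whether later use differs from a period in which they were hardly available, if at all.

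A significant result could then be read as support for the adoption hypothesis although use was flat, or had declined, after year 2. Pooling all post periods also mixes in year 5, which belongs to the sustainability question. At stake is one stated implementation hypothesis. The randomised patient comparison is not affected.

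**Working it through.** The article gives no adoption rate, number of treating providers or power for this outcome, so there is no planned figure to reproduce.

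**Inputs from the article**
- Hypothesised contrast: year 2 against years 3 and 4, upward (Background).
- Stated test: one-way repeated measures ANOVA, pre against all post (Analysis plan, Service delivery intervention).
- Pre-period: year 1, with years 2 to 5 as post (Background). Study design adds that the provider outcomes of the pre-post design are taken at study start and again at the end of year 1.
- Year 1 use of zero or near zero: an inference from Study setting, Background and Study design.
- Staff: 70 in all roles (Study participants).

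**Assumptions:** 25 treating providers, binary use per provider-year, year 1 use of 0, latent within-provider correlation 0.5, two-sided 5% level. Use rates are illustrative.

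**Step 1: what each comparison estimates.** With yearly use p1 to p4:
- pre against post: (p2 + p3 + p4)/3 − p1
- hypothesis: (p3 + p4)/2 − p2

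| Use in years 1, 2, 3, 4 | Pre against post | Hypothesised contrast |
|---|---|---|
| 0, 30, 30, 30% | 90/3 − 0 = +30 points | 30 − 30 = 0 |
| 0, 50, 30, 30% | 110/3 − 0 = +36.7 points | 30 − 50 = −20 points |
| 0, 30, 50, 50% | 130/3 − 0 = +43.3 points | 50 − 30 = +20 points |

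The first comparison is clearly positive in all three patterns. Only the second tells them apart.

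**Step 2: hand check of the flat 30% case.** Take a correlation of about 1/3 between a provider's yearly binary values. The variance of a provider's three-year mean is (0.30 × 0.70/3) × (1 + 2/3) = 0.1167, so the SD is 0.342. With 25 providers the standard error is 0.342/√25 = 0.068. The expected t is about 0.30/0.068 = 4.4, against a critical value of about 2.06 on 24 degrees of freedom.

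**Step 3: simulation, 25 providers, four yearly waves.** Overall test: F = [SS_year/(k − 1)] / [SS_error/((k − 1)(n − 1))], with k waves and n providers. Each contrast: t = mean(d)/(SD(d)/√n), where d is the provider's own contrast.

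| Pattern after year 1 | Overall F rejects | Pre against pooled post, significant | Hypothesised contrast, significant increase |
|---|---|---|---|
| Flat 30% | about 96% | 100% | about 4% |
| Falling 50, 30, 30% | 99.8% | 100% | 0% |
| Flat 20% | 66% | – | – |
| Flat 10% | about 20% | – | – |
| Flat 5% | about 6% | – | – |

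**Step 4: other sizes, five waves, comparable provider correlation.**
- Flat 30%: pre against pooled post was significant upward in 100% of runs at 20, 40 and 70 providers. The hypothesised contrast showed an increase in 2.9%, 3.4% and 3.1%.
- Falling 40, 30, 20, 10%: 99.7%, 100% and 100%, against 0.0% at each size.
- Flat 15% with 20 providers: the overall F rejected in 27% and the pooled contrast in 90%.
- Check, with 30% use in year 1 as well: both planned-type tests stayed near 5%. The positive results come from the near-zero starting level.

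**The case against.** The strongest reply is that the Analysis plan does not say which period is *pre* for adoption. The year 1 label is attached to other outcomes, and the article counts the pilot as part of the readiness intervention. The pilot year could therefore serve as *pre* for the service delivery intervention, which would be close to the hypothesis. This reading is possible, but no definition in the article supports it, and *all post* would still pool year 5 with years 3 and 4.

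Second, a repeated measures ANOVA over the years can carry a year 2 against years 3 and 4 contrast, and a fuller plan may contain one. That is true. But the article is not silent: it names the periods to be compared, and they are not those of the hypothesis.

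Three stronger readings are tempting, and the documents do not support them.
- *Any use at all would give a significant result.* At flat 5% to 10% use the overall F rejects in only about 6% to 20% of runs.
- *Year 1 adoption is zero by construction.* Study setting describes the clinic before the study. Year 1 included training, champions and universal screening with brief intervention, and adoption is partly self-reported. Zero or near zero is an inference, though a reasonable one.
- *Sustainability needs a test of year 5 against year 4.* The article asks only whether the practices are still in use in year 5. Lower but continuing use meets that hypothesis.

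Finally, adoption lies outside the randomised comparison, and the Discussion already discloses that providers were not randomised. This limits the consequence but does not repair the mismatch.

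**Conclusion.** The point holds as a mismatch between hypothesis and test: the stated comparison does not test growth in adoption from year 2 to years 3 and 4. That follows from the text and needs no simulation.

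How misleading the result could be depends on uptake. At moderate use, a significant finding is likely even when use is flat or falling after year 2. At low use the overall F test often would not reject, although the pooled contrast is more sensitive. These sizes rest on assumed use rates, an assumed number of treating providers and near-zero use in year 1. The plan should be corrected, but the randomised patient outcomes are untouched.

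**What to change.** Prespecify the mean of years 3 and 4 against year 2 as the adoption contrast. Fit it in a repeated-measures model suited to a binary or count outcome within provider, such as a logistic or count mixed model or GEE. The contrast is essential; the choice among these models is secondary. State which period is *pre* for each service system outcome, and report year 1 adoption descriptively. Report year 5 use separately as an estimate with a confidence interval, in line with the article's definition of sustainability.

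This changes wording and a contrast on data that the study already plans to collect. The price is power. With 25 providers, a rise from 30% to 50% is detected about 51% of the time. A rise from 15% to 35% is detected in 55%, 82% and 97% of runs with 20, 40 and 70 providers. All these rates are assumed. The article should give the number of treating providers and present the estimate with its interval, so that a non-significant result is not read as absence of growth.
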